### Sampling and recruitment strategies

Convenience sampling will be used. Potential study participants will be recruited through PD support groups and outpatient clinics. PD support groups will include the following: (1) the Hong Kong Society for Rehabilitation, a nonprofit rehabilitation organization serving over 100,000 members through its own primary-care facilities in Hong Kong and (2) Hong Kong Parkinson’s Disease Association, a PD patient support association serving over 1200 members.

Combinations of advertising strategies that have been found to be successful in prior recruitment initiatives for PD trials will be adopted [27–29]. These strategies will include printed flyers within the patient support centers and neurological clinics. Information will be disseminated through newsletters of patient support groups, which are expected to reach around 100,000 members. Enrollment will be further aided by collaboration with outpatient clinics, including the Pamela Youde Nethersole Eastern Hospital and the Prince of Wales Hospital. Potential participants will be referred by neurologists during their regular medical follow-up visits. Information and registration will be accessible online.

### Interventions

#### Experimental group

Participants in the experimental group will attend an 8-week structured yoga program. Each yoga session will last for 60 min and will be conducted in a group format once a week. There will be around 15–20 participants for each class to provide adequate instructional attention to each participant and to allow the yoga instructor to perform the required training routines. Participants will be encouraged to perform a 20-min, home-based practice twice a week (Table 1: yoga protocol).

**Table 1 Tab1:** Overview of the mindfulness yoga intervention

Week	1 − 2	3 − 4	5 − 6	7 − 8
Theme	Introducing mindfulness yoga to our body and life	Mindfulness of the body and content of mind		Loving-kindness and compassion
Breathing exercise (15 min)	Controlled breathing			
	Bee breath			
	Lion breath			
	Cooling breath			
	Alternate nostril breathing			
Mindfulness practice (15 min)	Mindfulness of breath and body meditation (body scan)	Mindfulness of body and thoughts meditation (body scan)	Mindfulness of feelings and movement meditation (mindful walking)	Loving-kindness and open awareness meditation (dyad practice)
Yoga practice (60 min)	Warm-up exercise (15 min)			
	Child pose			
	Cat and cow			
	Bridge			
	Lying hamstring stretch			
	12 poses of “sun salutation” with modifications (30 min)			
	Mountain pose			
	Upward salute pose			
	Standing forward bend			
	Lunge			
	Plank pose			
	Knees, chest, and chin pose			
	Cobra pose			
	Downward-facing dog pose			
	Lunge			
	Standing forward bend			
	Upward salute pose			
	Mountain pose			
	Cool-down exercise (15 min)			
	Child pose			
	Knee to chest			
	Corpse pose			
	Easy pose			

The dose of the yoga intervention took reference from the remarkable Mindfulness-based Stress Reduction (MBSR) program [30]. MBSR, which consists of eight weekly mindful yoga sessions, has been shown to be an effective behavioral intervention for people with stress, anxiety disorders, and chronic illness [31–33].

Twelve basic *Hatha* yoga poses, known as “sun salutations” (*surya namaskar*), with controlled breathing (*pranayama*) and mindfulness meditation (*dhyana*) will be taught. This set of yoga motions and postures is a gentle yet dynamic form of exercise that involves static stretching while exerting optimal stress on the cardiorespiratory system, and it has been described as the most complete yoga exercise [34]. During the mindfulness practice of yoga poses, participants will be taught to control their breathing and to envisage vital energy flowing freely between the body and mind, forming a deep connectedness to mind and spirit, reaching a state of equanimity.

#### Control group

To enhance the internal validity of the study, the participants in the control group will undergo weekly, 60-min stretching and resistance exercise and be encouraged to perform a 20-min, home-based practice twice a week for 8 weeks (Table 2: stretching and resistance exercise protocol). Current evidence shows that both stretching and resistance exercises and yoga improve motor symptoms and functions in the PD population [19, 35]. Since the former only focused on physical wellbeing, it has been chosen for the control group. The set of stretching and resistance exercises was modified from a previously validated study for older adults with osteoarthritis [36]. A fitness instructor will be recruited to deliver the intervention. These regular gatherings will be aimed at balancing the psychosocial effect of the weekly gathering of the experimental groups during the study period. No information relating to yoga, mindfulness meditation, and psychological wellbeing will be covered in stretching and resistance exercise classes. One class will have approximately 15–20 participants.

**Table 2 Tab2:** Overview of the stretching and resistance exercise intervention

Week	Warm up	Resistance training	Stretching and cool down
1 − 2	Seated: Straight arm forward rotation^1^ Straight arm backward rotation^1^ Straight arm up-and-down flapping^1^ Seated forward and backward stepping^1^ Seated hip abduction and adduction stepping^1^ Seated knee raise^1^	Seated: Seated forward leg extension^1^ Seated backward leg curl^1^ Standing^a^: Single leg knee raise^2^ Alternate knee raise^1^ Mini squat (30°)^1^	Seated: Seated hamstring stretch^2^
3 − 4	Seated: Straight arm forward rotation^1^ Straight arm backward rotation^1^ Straight arm up-and-down flapping^1^ Straight arm horizontal abduction and adduction^1^ Trunk rotation and hold^1^ Standing^a^: Straight leg forward kick^1^ Straight leg backward kick^1^ Straight leg hip adduction and abduction^1^ Alternate knee raise^1^	Seated: Straight leg forward kick^2^ Straight leg circling^2^ Standing^a^: Calf raise^2^ Mini squat (45°)^2^	Standing^a^: Hamstring stretch^2^ Calf stretch^2^
5 − 6	Seated: Straight arm forward rotation^1^ Straight arm backward rotation^1^ Straight arm up-and-down flapping^1^ Straight arm horizontal abduction and adduction^1^ Trunk rotation and hold^1^ Standing^a^: Straight leg forward kick^1^ Straight leg backward kick^1^ Straight leg hip adduction and abduction^1^ Alternate knee raise^1^	Seated: Straight leg circling^2^ Straight leg alternate crossover^2^ Standing^a^: Single leg standing^2^ Single leg calf raise^2^ Wall squat^2^	Standing^a^: Hamstring stretch^2^ Calf stretch^2^ Upper trapezius stretch^2^
7 − 8	Seated: Straight arm forward rotation^1^ Straight arm backward rotation^1^ Straight arm up-and-down flapping^1^ Straight arm horizontal abduction and adduction^1^ Trunk rotation and hold^1^ Standing^a^: Straight leg forward kick^1^ Straight leg backward kick^1^ Straight leg hip adduction and abduction^1^ Alternate knee raise^1^	Standing^a^: Single leg standing^2^ Single leg calf raise^2^ Side lunges^2^ Wall squat^2^	Standing^a^: Hamstring stretch^2^ Calf stretch^2^ Upper trapezius stretch^2^ Side trunk flexion stretch^2^ Forearm stretch^2^

^a^Standing with hands rest on chair back; ^1^10 s, two cycles, with 10 s rest; ^2^20 s, two cycles, with 10 s rest

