### Sample size

According to a meta-analysis of the effects of yoga on depression compared with aerobic exercise, a moderate effect size of 0.59 was reported for individuals with elevated levels of depression.

In addition, a moderate-to-large effect size of 0.79 on anxiety was found when comparing yoga with relaxation [26]. To anticipate the effect size of at least 0.59 for our primary outcomes (depression and anxiety) and using the power analysis software Gpower 3.1, 47 subjects per arm give a two-arm RCT 80% power to detect an effect size of at least 0.59 at 5% level of significance. Considering previous RCTs of mind-body interventions among people with PD [20], an attrition rate of 25% is taken into consideration. Therefore, 126 subjects with 63 per arm will be recruited.

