### Data analysis

Descriptive statistics will be used to summarize the demographic, health conditions and clinical outcomes of the participants at three different time points. Normality of the variables will be assessed using the skewness statistic and normal probability plot. The two treatment groups will be examined, at baseline (T0), after the completion of intervention (T1), and 3 months after the completion of intervention (T2), for the changes in psychological distress, motor symptoms, mobility and balance, spiritual wellbeing, and HRQoL among participants. The intention-to-treat principle will be applied in all analyses. The intervention arm will be compared against the control for all primary analysis. Generalized estimating equation (GEE) models, specific with first-order, auto-regressive structure, will be used to assess the differential change of each primary outcome variable (HADS) and secondary outcome variable (MDS-UPDRS-III, TUG, HWS, and PDQ-8), across different time points between the two groups. Completers and noncompleters will be compared to examine any difference in demographic characteristics and health conditions. Prespecified subgroup analyses by gender, level of education, disease staging, and the presence of psychological distress will be conducted. IBM SPSS 22.0 software will be used for statistical analysis. All statistical tests will be two-tailed and statistical significance will be set at 0.05. The final report will follow the CONSORT 2010 guidelines as well as its extension to nonpharmacological interventions.

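### Both arms are treated in classes of about 15–20, but the 80% power and the planned GEE assume independent participants; if classmates' outcomes correlate, standard errors are too small and 80% is optimistic

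*Protocol article*

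**What the plan says.** Individuals are randomised 1:1 in blocks of 8 (Randomization and allocation concealment). Treatment is then given in weekly groups for 8 weeks. Under Experimental group: "There will be around 15–20 participants for each class". Under Control group: "One class will have approximately 15–20 participants".

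The Sample size section states that "47 subjects per arm give a two-arm RCT 80% power to detect an effect size of at least 0.59 at 5% level of significance". It adds that "an attrition rate of 25% is taken into consideration", which gives 63 per arm and 126 in total. It mentions no intraclass correlation and no design effect.

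The Data analysis section names "Generalized estimating equation (GEE) models, specific with first-order, auto-regressive structure" for HADS and the secondary outcomes, comparing the two groups over the three assessments. It names no class term. On error rates it says "All statistical tests will be two-tailed and statistical significance will be set at 0.05".

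**The concern.** Classmates share peers, place and time slot for 8 weeks, and the primary outcome is self-reported anxiety and depression. The protocol itself expects meeting as a group to matter: the control classes are partly there to offset the psychosocial effect of the yoga group's weekly meetings. Holding classes in both arms balances the average of that effect between arms. It does not remove the correlation among people in the same class.

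A first-order autoregressive structure is ordered by time, so it describes repeated measurements on one person. A robust variance clustered on the participant still treats classmates as independent. If the class-level correlation is positive, confidence intervals for yoga against exercise are too narrow and false positives exceed 5%, in favour of finding a difference. The stated 80% power also describes a precision that the grouped design does not deliver.

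**Working it through.** **Inputs from the protocol article.** Effect size 0.59, 47 evaluable per arm, 80% power and 25% attrition (Sample size); two-sided 5% (Data analysis); 15–20 per class (Interventions). **Assumed:** ICC of 0.01, 0.02 or 0.05.

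**1. The plan's own figure.** A two-sample t-test (noncentral t, two-sided 5%, effect size 0.59) has 80.8% power at 47 per arm and 79.9% at 46. Then 47/0.75 = 62.7, rounded up to 63 per arm, 126 in total. The stated figures reproduce exactly with a design effect of 1.

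**2. Number and size of classes.** 63/20 = 3.15 and 63/15 = 4.2, so about 3–4 classes per arm. At the midpoint of 17.5 enrolled and 75% retained, 17.5 × 0.75 = 13.1 are analysed per class.

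**3. Design effect.** DE = 1 + (13.125 − 1) × ICC. The true standard error is √DE times the one that assumes independence.

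**4. Two separate consequences.** They belong to different tests and should not be read as a pair.

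- *A test that ignores class.* Type I error = 2 × [1 − Φ(1.96/√DE)]. Its rejection rate at the assumed effect is Φ((2.860 − 1.960)/√DE), where 2.860 = 0.59 × √(47/2). With DE = 1 this is 81.6% (normal approximation).
- *A valid test that allows for class.* Noncentrality 2.860/√DE, evaluated first on 92 degrees of freedom, that is, with no loss for the small number of classes.

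| ICC | DE | √DE | Ignoring class: type I error | Ignoring class: rejection at 0.59 | Allowing for class: power, no df loss |
|---|---|---|---|---|---|
| 0 | 1.00 | 1.00 | 5.0% | 82% | 81% |
| 0.01 | 1.12 | 1.06 | 6.4% | 80% | 76% |
| 0.02 | 1.24 | 1.11 | 7.9% | 79% | 72% |
| 0.05 | 1.61 | 1.27 | 12% | 76% | 61% |

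Over the stated class range, 25% attrition leaves 11.25–15 per class. At ICC 0.05 that gives DE 1.51–1.70 and power 63–58% in the last column.

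**5. Cost of having few classes.** Six to eight classes in total leave only about 4–6 class-level degrees of freedom. A random-class model with Satterthwaite degrees of freedom was simulated at one time point, with 3 classes of 16 or 4 classes of 12 per arm and the class variance not allowed below zero. Power was about 61–67% at ICC 0, 56–63% at 0.01, 51–59% at 0.02 and 40–50% at 0.05. The lower end is 3 classes per arm, the upper end 4. At ICC 0.01 the class variance was estimated as zero in about half the runs.

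**6. Better retention.** If all 63 per arm were analysed in classes of 17.5, DE = 1 + 16.5 × ICC, or 1.165, 1.33 and 1.825. Without clustering, power would be 90.8%. At ICC 0.02 it is about 81% before df loss. The type I error of a test that ignores class would be 6.9%, 8.9% and 14.7%, so it does not improve.

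**The case against.** - **The correlation may be negligible.** The document gives no ICC, and at ICC 0 the stated 80% is right. This stands, and the point must be put conditionally.
- **The article is condensed.** An analysis plan that is not shown could add a class term, and the Data analysis section does not exclude one. This also stands. It cannot change the published basis for the 80%, which is an independence calculation.
- **The t-test is not the planned model.** The GEE uses baseline and repeated measurements, whose within-person correlation is not given, so its power differs from 80.8% even without clustering. True, but that does not make classmates independent.
- **Instructor effects are not clearly class effects.** Both arms are described with a single instructor. If one person teaches all classes in an arm, the instructor effect is confounded with arm and is not part of the between-class variance. A random class effect would not capture it. Peers, place and timing remain.
- **The class-aware model is costly.** With 6–8 classes it loses roughly 15–20 points of power even if there is no clustering. This stands, and is why making it the sole primary analysis is a trade-off and not an obvious correction.

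A reader might infer that the planned GEE itself would detect the assumed effect only 61–76% of the time. The arithmetic does not support that. A test that ignores class still rejects about 76–80% of the time at these ICCs; its main fault is false positives. The lower figures describe a test that controls the error rate.

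**Conclusion.** The point holds in conditional form. Treatment in about 3–4 classes per arm is stated, the sample size is an independence calculation, and the stated correlation structure covers only time within a person. For any positive class ICC, the planned standard errors are too small and the 80% is overstated.

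The size rests on the assumed ICC range of 0.01–0.05, about 13 analysed per class and 47 per arm. Type I error is about 6.4% to 12% if class is ignored. Power is at most about 76% down to 61% if class is allowed for, and about 56–63% down to 40–50% once the few classes are reflected in the degrees of freedom. Retention above 75% would recover part of the power but would not repair the type I error. The structural omission is certain; its numerical effect is not.

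**What to change.** 1. Record a class identifier for every participant in both arms. Instructors already check attendance, so the information is at hand.
2. Prespecify a class-aware analysis of HADS, for example a mixed model with a random class effect and Satterthwaite degrees of freedom, which the planned SPSS software offers. Report it beside the GEE at least as a sensitivity analysis, with the estimated ICC, and interpret a significant GEE result in its light. Simply making class the GEE cluster would itself need a small-sample correction with so few classes.
3. Restate the Sample size section: 80% power applies only if participants are independent, followed by power over an assumed ICC range that includes the loss of degrees of freedom.

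The cost is one extra variable and revised text. The class-aware analysis will have noticeably wider intervals and lower power, and the stated power becomes less favourable. No extra recruitment is required.

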### Validity and reliability

#### Content validity

To assure the validity of the novel mindfulness yoga intervention, including appropriateness, safety, and applicability, the yoga protocol was reviewed by a representative panel of seven experts with clinical expertise, including one neurologist, one PD nurse specialist, one physical education researcher specialized in balance and fall, one physiotherapist, one occupational therapist, and two yoga instructors, both of whom are experienced in teaching people with chronic illnesses and one of them is a certificated “Mindfulness-based Cognitive Therapy” (MBCT) and “Mindfulness-based Stress Reduction” instructor.

The yoga protocol has been validated. The content validity of each items of intervention was estimated by the Item-Content Validity Index (I-CVI), which guided the decisions of item revisions or rejections. An I-CVI of 0.78 or higher was considered good content validity [37]. Meanwhile, comments from experts guided the development of any new item and amendment of existing items.

Two rounds of panel review were conducted. During the first round, among the 20 poses, the following modifications were made according to expert’s opinions:The axial rotation in reclined spinal twist pose was considered as less relevant to be one of the warm-up exercises of the yoga practice (sun salutations). This pose was replaced by the child pose, which can gently stretch the shoulders, neck, back, hips, thighs, and anklesStanding forward bend and downward-facing dog poses might be too difficult for participants with postural instability. Therefore, these two poses were modified as keeping the feet hip-distance wide and bending the knees to make it easier for those beginners or participants with postural instabilityAn inquiry was raised to determine as to whether the corpse pose was a kind of meditation. Actually, it is a common cool-down exercise of yoga, which positions the body in a neutral position of rest and relaxation. Thus, this pose remained unchanged with the purpose of enhancing one’s mindful awareness of breath, body, and mind

In the second round, the I-CVIs of all poses reached 1.0. The finalized protocol of the yoga intervention is listed in Table 1.

#### Randomization and allocation concealment

Eligible participants will be randomized into the experimental or the control group with an allocation of 1:1 by using a computer-based permuted block randomization with a block size of 8. The randomization sequence will be generated by an independent research assistant. Details of the group allocation will be concealed on cards inside a sequentially numbered series of sealed opaque envelopes. The envelopes will then be submitted to a research coordinator responsible for contacting participants and allocating them to their assigned group.

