### Design

The study will be a single-blinded randomized controlled trial (RCT). Eligible participants will be randomized into experimental or control groups at 1:1 ratio through a permuted block randomization with a block size of 8 [25]. Figure 1 shows the Consolidated Standards of Reporting Trials (CONSORT) flow diagram, schedule of enrollment, interventions and assessments of the study, Fig. 2 shows the Standard Protocol Items: Recommendations for Interventional Trials (SPIRIT) Figure and Additional file 1 the SPIRIT Checklist utilized in the study.

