#### Blinding

This will be a single-blind RCT. The outcome assessor will be blinded to the subject allocation. The outcome assessor, who is independent from group allocation, will be responsible for outcome measurement. However, it would be hard to blind the participants given the nature of the intervention. This single-blind design may potentially expose the study to risks of bias in terms of performance, attrition, and evaluation and so inflate the treatment effects if the participants know their group allocation. Although blinding the participants to intervention assignment will be inapplicable in this study, various strategies will be used to minimize these risks. To minimize bias stemming from expectation, study participants will be blinded to the study hypotheses and details of study manuals, the information provided in the Informed Consent Form will follow the principle of equipoise by declaring uncertainty about the superiority of treatment effect of both arms [38]. Similar expected outcomes, such as improving general wellbeing, will be stated in the Information Sheet for both experimental and control groups. All participants will receive the same number of sessions of intervention and assessment. The participants will be reminded not to disclose their group status to the study assessor at any time point. This method is widely used to mask the outcome assessor from treatment assignment as recommended by the Evidence-based Behavioral Medicine Committee [39].

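### A single fixed block size of 8 lets anyone who knows it and tracks past allocations foresee about one allocation in five; randomly varying, withheld sizes would remove most of this at almost no cost

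*Protocol article*

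**What the plan says.** Under Design, participants are assigned "at 1:1 ratio through a permuted block randomization with a block size of 8". Under Randomization and allocation concealment the rule is repeated as "computer-based permuted block randomization with a block size of 8". Neither section mentions varying sizes, strata, or keeping the size from study staff.

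The same section says that an independent research assistant generates the sequence and that allocations are "concealed on cards inside a sequentially numbered series of sealed opaque envelopes". It then continues: "The envelopes will then be submitted to a research coordinator responsible for contacting participants and allocating them to their assigned group". Under Data collection, eligibility screening belongs to the principal investigator. Under Blinding, only the outcome assessor is masked; for participants, the article says "it would be hard to blind the participants given the nature of the intervention".

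**The concern.** A sealed envelope stops someone from reading the next card. It does not stop someone from working out the next card from those already opened. With a known block of 8 at 1:1, once either arm has filled its four places, every remaining card in that block is determined. The coordinator allocates from a numbered series in an open-label setting and so is placed to see the past allocations in order. The coordinator also contacts participants, and so may have some influence on the order or timing of entry.

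At stake is selection. Recruitment is by convenience sampling, the second hypothesis is that yoga is superior, and the primary outcome is a scale of anxiety and depressive symptoms in people who know their arm. If foreknowledge affected who entered when, the arms could differ at baseline in distress or motivation, which bear directly on that outcome.

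**Working it through.** **Inputs.** Block size 8 and ratio 1:1 (Design; Randomization and allocation concealment). Total 126, and 47 evaluable per arm for 80% power at an effect size of 0.59 (Sample size). Two-sided 5% level (Data analysis). The article gives no predictability figure to reproduce. Its sample size does reproduce: a two-sample t-test with 47 per arm has power 0.808, and 47/0.75 = 62.7, so 63 per arm and 126 in total.

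**Certain allocations in one block of 8.** There are C(8,4) = 70 equally likely blocks. Position k is certain if one arm filled its four places in the first k − 1 positions, which has probability 2·C(k−1,4)/70:

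- Positions 1 to 4: 0
- Position 5: 2/70 = 2.9%
- Position 6: 10/70 = 14.3%
- Position 7: 30/70 = 42.9%
- Position 8: 70/70 = 100%

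The sum is 112/70 = 1.6 per block, or 1.6/8 = 20%. The closed form for block size 2m, 2m/(m+1), gives 8/5 = 1.6 for m = 4.

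**Over 126 participants.** 126 = 15 × 8 + 6, so there are 15 full blocks and six places of a sixteenth. The expected number of certain allocations is 15 × 1.6 + (2 + 10)/70 = 24 + 0.17 = 24.2, and 24.2/126 = 19.2%.

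**Best-guess success.** Always guessing the arm with more places left is right in a share [m + (4^m/C(2m,m) − 1)/2]/(2m). For m = 4 this is [4 + (256/70 − 1)/2]/8 = 5.33/8 = 66.6% per block. Enumeration over the 126 places gives 83.5/126 = 66.3%. Simple randomization gives 50%.

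**Randomly varying sizes.** Sequences of 126 were simulated with block sizes drawn with equal probability. The observer was assumed to know the candidate sizes but not the draws, and to update exactly on the full history.

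| Block sizes | Certain allocations | Best guess right |
|---|---|---|
| 8 only | about 19% | about 66% |
| 4, 6, 8 | about 2% | about 68% |
| 6, 8, 10 | about 1.5% | about 66% |
| 8, 10, 12 | about 1.3% | about 65% |

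Varying the size removes most of the certainty but hardly changes guessing. Small sizes make guessing slightly easier, so the larger set is preferable.

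**Cost in balance.** With fixed blocks of 8, six places of the last block are used, so the final split is 63/63 (probability 40/70 = 57%) or 64/62. With 8, 10 and 12, the worst case is stopping after six same-arm places in a block of 12, which gives 66/60. A difference of 6 among the 94 evaluable participants (50/44) has power 0.806, against 0.808 at 47/47.

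**The case against.** The strongest reply is that selection bias needs one person who both foresees the arm and influences who enters. The article separates these roles: the principal investigator screens, an independent assistant generates the sequence, and the coordinator allocates people already found eligible. Nothing shows that the screener sees the running allocations. This stands and limits the risk, although the order and timing of contact remain with the coordinator.

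The 20% also assumes that allocation is one at a time, that earlier allocations are tracked in order, and that the size is known. Classes of 15–20 make allocation in cohorts plausible, which would reduce the exposure. The article does not say whether this is done, nor whether the coordinator knows the block size. These are conditions on the figure.

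The procedure is otherwise sound and the two sections agree with each other. But the block size is a stated choice, not a detail left to a fuller document, and neither envelopes nor an independent generator blocks deduction from past cards.

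Two stronger readings are tempting and not supported:

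- A reader might infer that publishing the block size created the exposure. The article is dated 2 November 2017. Completion was expected by March 2018 with the last assessment at week 20, so randomization would have to end between about mid-October and mid-November 2017. Few allocations could follow publication; the relevant route is staff knowledge of the working protocol.
- A reader might infer that a few disclosures would unblind the assessor for other participants. The assessor is independent of allocation and participants are told not to disclose. Certainty would need the enrolment order, the block boundaries and four same-arm disclosures within one block.

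**Conclusion.** The point holds as an avoidable weakness in a stated rule. For a person who knows the size and tracks allocations singly, an expected 20% per block, about 24 of 126 (19%), are certain before opening. That is an upper figure: it falls if the size is not known to the coordinator or if cohorts are allocated together. It is tempting to conclude that concealment was broken or that the HADS comparison is biased. The documents show neither, and no size of bias can be derived from them. The change is worth making because it removes nearly all certain allocations at almost no cost, but it is not a remedy for guessing, which stays near 65%.

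**What to change.** Under Design and under Randomization and allocation concealment, replace the fixed size of 8 with randomly varying block sizes, for example 8, 10 and 12, withheld from the principal investigator, the research coordinator and the assessor until the trial ends. Withholding matters as much as varying, because best-guess success barely moves when the candidate sizes are known. If envelopes are opened by class cohort, say so, since this further limits the exposure. If enrolment is already complete, report who knew the block size and whether allocation was one at a time.

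The cost is a few lines in the randomization program and a sentence in each section. The worst-case final split widens from 64/62 to 66/60, which changes power by about 0.002.
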